## Abstract

Chronic migraine (CM) is a highly disabling condition, affecting about 2% of the global population. Non-pharmacological treatments can be optimal for their non-invasive nature. This prospective, randomized, double-blind, controlled trial aimed to test the efficacy of therapeutic neuroscience education (TNE) in CM. Early response biomarkers were also evaluated. A total of 80 CM patients were consecutively enrolled and randomly allocated to TNE or a general education program. Treatment effectiveness was evaluated at baseline (T1) and 2 months after the end of treatment (T4). We collected the responses to disability and comorbidity questionnaires at the start (T1) and end of treatment (T3, 10 weeks after start). Early response biomarkers were evaluated at screening (T0) and mid-way through the process (T2, 5 weeks after start). We expected that TNE would provide a greater benefit than the general education program, which served as the primary outcome of this study. We also expected that a change in clinical and neurophysiological measures could potentially occur, reflecting plasticity-induced reorganization and predicting clinical response. This is the first study selectively exploring the effect of TNE as a standalone treatment for CM. A new, effective treatment regime without interactions with other medication could be of great interest as an addition to migraine therapeutic strategies.

## 1. Introduction

Migraine represents the seventh most common cause of disability in the global population and the first cause of disability in adults under 50 years of age [1]. Compared to the episodic form, chronic migraine (CM), i.e., >15 days/month, entails a greater disability, lower individual productivity, worse quality of life, and larger expenses (an average of EUR 2250 ± 1796 per person per year) [2,3]. CM affects 2% of the global population, and half of patients with headache are referred to specialized headache centers [4,5]. About 3% of episodic migraineurs convert to CM every year [6], with the most important risk factors being obesity, depression, stressful life events, and overuse of symptomatic medication, which constitutes medication-overuse headache (MOH) [4].

To date, pharmacological treatments represent the mainstay of the therapeutic management of CM, with non-pharmacological (e.g., neuromodulatory [7], rehabilitative [8], or psychotherapeutic [9,10]) approaches remaining less frequently utilized because they are supported by a lower level of evidence [11].

However, the success rate of preventive pharmacological therapies is lower than 50% for CM [12] because of drug inefficacy, frequent side effects, comorbidities, or drug-to-drug interactions [12,13,14]. Monoclonal antibodies, released on the market in recent years, are very effective but limited in prescription by their high cost, either for private or public health systems.

Interestingly, while comorbidities generally represent a drawback for the pharmacological management of CM, this is not always true for some non-pharmacological approaches, such as neuromodulation and psychotherapy, where some comorbidities are positively correlated with clinical benefits [15], suggesting that non-pharmacological options can have a role in treating patients with complications.

Therapeutic neuroscience education (TNE) is a non-pharmacological approach with some level of evidence for migraine management, although the exact parameters (e.g., delivery methods, number of sessions) remain to be elucidated [16,17,18].

TNE is defined as an “educational program aimed at improving the comprehension of pain mechanism, enhancing the coping strategies and increase the patients’ quality of life” [19]. In contrast, conventional anatomical and biomedical education not only showed limited or no efficacy in decreasing pain and disability in patients but might even increase fear, catastrophizing, and pain levels, inducing a nocebo effect [20]. TNE aims to increase knowledge of pain neurophysiology and neurobiology, pain representation, and the meaning of pain and to improve coping strategies [21,22,23]. It also shows effectiveness in reducing pain intensity and migraine disability and improving patients’ moods, with a positive clinical benefit in terms of pain rating, pain-related disability, catastrophizing, and physical performance [24,25] when applied to patients with chronic musculoskeletal pain.

Functional magnetic resonance studies showed that TNE exerts an effect by reducing the activity of several areas belonging to the cerebral pain network [21], suggesting that this intervention could be monitored by neural biomarkers.

Migraine prevention generally requires several months of treatment, either with pharmacological or non-pharmacological therapies. Therefore, a predictive marker could be of great interest, since an early change occurring before the effect of treatment could help in selecting patients or reducing the time of administration of the treatment itself if unnecessary.

Several available and easy-to-perform neurophysiology techniques can be used to highlight the benefit of systemic [26], local [27], and neuromodulatory [7] treatments for migraine. The intensity dependence of auditory-evoked potentials (IDAP), a non-invasive measurement of serotonergic firing from brainstem to cortex, predicted recovery from chronic to episodic migraine after the administration of a single greater occipital nerve block [27].

Also, the nociceptive blink reflex (nBR) was found to be sensitive to changes in excitability induced by transcranial magnetic stimulation and flashlight, biofeedback, and some medications [28,29,30].

Clinically, quantitative sensory testing (QST) was found to effectively assess somatosensory function and differentiate between various phases of the migraine cycle, as responses to different stimuli vary throughout these phases [31].

The primary objective of this study is to evaluate the efficacy of TNE as a preventive treatment for CM compared to a general education protocol, with a focus on reducing monthly headache days from baseline to follow-up. Additionally, we aim to identify potential predictive factors through neurophysiological assessments.

The primary outcome is the reduction in migraine days, as the observed improvement should be at least comparable to that achieved with other therapies. Accurately predicting TNE effectiveness at baseline or early in the treatment process will help identify patients with a high likelihood of response, ensuring they receive appropriate long-term, high-commitment care.

We hypothesize that TNE will reduce monthly headache days and that mid-treatment changes in IDAP, nBR, and QST assessments will precede clinical improvement, serving as potential biomarkers.

## 2. Materials and Methods

### 2.1. Study Cohort

Consecutive CM patients will be recruited for the study. Eligibility criteria will include a CM diagnosis (with or without MOH) based on the International Classification of Headache Disorders (ICHD-3) criteria [32] and age > 18 years, as recent data suggest TNE is effective in older adults as well [33]. Patients will be enrolled consecutively. Exclusion criteria will include an ICHD-3 diagnosis of another primary or secondary headache disorder (except for MOH), neurological or psychiatric conditions that could affect compliance or neurophysiological assessments (e.g., neurodegenerative disorders, multiple sclerosis, epilepsy, schizophrenia, severe anxiety/depression with HADS >15), chronic pain conditions (e.g., low-back pain, chronic pelvic pain), severe comorbidities related to migraine or systemic diseases requiring concurrent medical treatment, and malignancy. Patients on migraine preventive therapy will be included if their prophylaxis has remained unchanged and ineffective for at least three months prior to recruitment. This treatment will not be down-tapered or discontinued at the study’s onset. Relevant demographic data will also be collected.

Migraine burden will be assessed throughout the study using a headache diary (tracking headache days, pain intensity, and acute medication use) and several validated questionnaires, including the Migraine Disability Assessment (MIDAS), the Headache Impact Test (HIT-6), the Central Sensitization Inventory (CSI), the Pain Catastrophizing Scale (PCS), and the Hospital Anxiety and Depression Scale (HADS) [34,35,36,37,38].

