### 2.2. Outcome Measures

The primary aim of the present study is to test the efficacy of TNE as a preventive treatment for CM compared to a general education protocol. The primary outcome will be the reduction in monthly headache days from baseline to follow-up. Secondary endpoints will include (i) the interruption rate of MOH; (ii) the proportion of patients achieving a >50% reduction in headache days (i.e., responders) at follow-up; (iii) differences in biomarkers (IDAP, nBR, and the QST) between responders and non-responders, along with the correlation between these biomarker values and clinical improvement in headache day reduction to assess their potential as efficacy predictors; and (iv) significant reductions in disability and migraine burden scores.

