### 2.3. Randomization, Schedule, and Adherence

Patients will be randomly assigned at a 1:1 ratio using a pre-generated randomization list created in SPSS by an experimenter who will not be involved in patient recruitment, treatment, or data analysis. Participants will be required to attend a full course of 10 lessons, with the first and last sessions conducted in person and the remaining eight delivered remotely via PowerPoint presentations. Lessons will be held in small groups, with the real and control education groups scheduled on different days to prevent interaction between participants from different study arms. The treatment will be considered valid if patients attend at least 8 out of 10 lessons. In case of absence, the PowerPoint presentation from the missed session will be sent to the participant. Additionally, a brief Q&A session will be conducted before the next lesson to review the content and address any questions.

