### 2.10. Plans for Analysis

An a priori calculation of the sample size was performed based on the primary endpoint. In line with studies on CM with MOH, we aim for a between group difference of 3.0 monthly headache days at T4 and a standard deviation of 4.5 [55]. Using an alpha error of 5%, a power of 80%, and a medium effect size, the calculated sample size is 70 patients. Considering a reasonable dropout rate, we plan to recruit 80 patients.

To assess the treatment’s effects on clinical and instrumental outcomes, a generalized linear mixed model for repeated measures (*p*-value < 0.05) will be performed on the primary outcome and, in a sub-analysis, on secondary outcomes. The model will include group and time as fixed effects, time by group as an interaction term, and the outcome as the dependent variable. Covariates will be selected from those identified as significantly different between groups [10]. A correlation analysis will also be conducted between migraine disability indexes and clinical/neurophysiological measures to identify potential biomarkers. False discovery rate correction will be applied to reduce type-I errors.

The number of adverse events (AEs) during the treatment period will be counted separately for the TNE-A and CON-A groups and classified according to common terminology criteria for adverse events (CTCAEs). An AE is defined as any adverse medical event associated with the use of a treatment in humans, regardless of whether it is considered related to the treatment. Causality (relationship to study treatment), action taken, and outcome will be summarized separately.

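### Baseline MOH status should be a pre-specified term in the primary model: the significance-based covariate rule would almost never admit it, although the cohort mixes patients with and without MOH

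*Protocol article*

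**What the plan says.** Section 2.1 makes MOH neither a requirement nor a bar to entry: "Eligibility criteria will include a CM diagnosis (with or without MOH"). The exclusion for other headache disorders repeats the exemption: "another primary or secondary headache disorder (except for MOH"). No proportion of MOH patients is expected or capped.

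Section 2.10 draws its planning figures from one part of that population: "In line with studies on CM with MOH, we aim for a between group difference of 3.0 monthly headache days at T4", with "a standard deviation of 4.5". The resulting size is stated as "Using an alpha error of 5%, a power of 80%, and a medium effect size, the calculated sample size is 70 patients", raised to 80 for dropout.

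Section 2.3 describes allocation as follows: "Patients will be randomly assigned at a 1:1 ratio using a pre-generated randomization list created in SPSS". It names no stratification factor.

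Section 2.10 also sets out the primary model. Group, time and their interaction are the fixed terms. Any further covariate is drawn from the variables on which the arms prove to differ significantly. MOH status is not named. It is nevertheless a characteristic the trial uses elsewhere: the first secondary endpoint in section 2.2 is "the interruption rate of MOH".

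**The concern.** MOH status is established when the eligibility diagnosis is made, so it is available before randomisation at no extra effort. If patients with and without MOH differ in how much their headache days fall, the difference adds to the spread of the primary outcome unless the analysis accounts for it.

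The stated covariate rule does not do this. It asks whether the arms differ on MOH by a significance test. What matters for precision is whether MOH predicts the outcome. With arms of 40 the test detects only large imbalances, so a prognostic factor would nearly always be left out, and it would come in only after the arms had been inspected.

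The size calculation leaves little room for this. Seventy analysed patients give slightly under 80% power on the plan's own inputs, and those inputs come from CM with MOH without any reason given for applying them to a mixed cohort.

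**Working it through.** **1. The plan's sample size.** Inputs from section 2.10: difference 3.0, SD 4.5, alpha 5% (two-sided assumed, as the text does not say), power 80%.

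n per arm = 2 × [4.5 × (1.960 + 0.842) / 3.0]² = 35.3.

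Rounded up this is 36 per arm, 72 in total, so the stated 70 is reproduced to within two patients. At 35 per arm the power is 79.6% by the normal approximation and 78.5% by the t test. The t-test figure is the reference below.

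**2. How often the covariate rule would admit MOH.** Assumptions: 80 patients split 40/40; 24, 40 or 56 of them with MOH (30%, 50%, 70%); an uncorrected chi-square test at 5%. The number of MOH patients in one arm is then hypergeometric.

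| MOH share | 20-point imbalance | p | 25-point imbalance | p | Probability that the rule admits MOH |
|---|---|---|---|---|---|
| 30% | 16 v 8 | 0.051 | 17 v 7 | 0.015 | 2.7% |
| 50% | 24 v 16 | 0.074 | 25 v 15 | 0.025 | 4.4% |
| 70% | 32 v 24 | 0.051 | 33 v 23 | 0.015 | 2.7% |

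An imbalance of 20 points or more arises in 9% to 12% of such allocations, but exactly 20 points does not reach significance at any of the three shares. The rule acts only from 25 points upward.

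**3. What leaving MOH out would cost.** Let p be the MOH share and g the gap in mean change in headache days between patients with and without MOH. The documents give neither. Take 4.5 as the SD within each MOH group, which is a further assumption. The SD that the unadjusted comparison faces is

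SD = √[4.5² + p(1 − p)g²].

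For p = 0.5 and g = 3: √(20.25 + 0.25 × 9) = √22.5 = 4.74. Power is from the noncentral t distribution, difference 3.0, two-sided 5%:

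| Gap g (days, assumed) | SD | Power, 35 per arm | Power, 40 per arm |
|---|---|---|---|
| 0 | 4.50 | 78.5% | 83.8% |
| 1 | 4.53 | 78.0% | 83.3% |
| 2 | 4.61 | 76.5% | 82.0% |
| 3 | 4.74 | 74.2% | 79.8% |
| 5 | 5.15 | 67.1% | 73.0% |

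At p = 0.3 or 0.7 the loss is slightly smaller (g = 3 gives SD 4.71).

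**4. The same loss within one allocation.** An imbalance of d in MOH share moves the estimated arm difference by d × g. At 20 points and g = 3 this is 0.2 × 3 = 0.6 days, against a target of 3.0. This is the variance in step 3 seen in a single trial and must not be added to it.

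**5. Which model term is needed.** The treatment effect is the group-by-time contrast, in other words a difference in change. A constant difference in headache days between MOH and non-MOH patients cancels from that contrast. A main effect of MOH alone would therefore not adjust the change; the MOH-by-time interaction does.

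**The case against.** Four objections have force.

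- **The list may be stratified.** A reader might infer from section 2.3 that randomisation is unstratified. The text does not say so. It is a condensed article, and strata and blocks are details that such an article often omits. All that can be said is that no stratification by MOH is described. The covariate rule is different, because the article states it outright.
- **The SD need not be larger in the mixed cohort.** A reader might infer that enrolling non-MOH patients must inflate the SD above 4.5. That depends on the unknown SD among non-MOH patients. If it were 4.0, with half the cohort having MOH and a 3-day gap, the pooled SD would be √(0.5 × 20.25 + 0.5 × 16 + 0.25 × 9) = 4.51, practically the planned value. With 3.5 it would be 4.30. What stands is that any gap in change adds avoidable variance if it is not modelled.
- **Chance imbalance is not bias.** Randomisation leaves the comparison unbiased on average and the type I error intact. Imbalance and extra variance are one loss of precision, not two harms.
- **The size is assumed.** At a gap of 2 days or less the loss is about 2 points of power or less, and the t-test figures only approximate the planned repeated-measures model.

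Nor is there a separate defect in the MOH endpoint or in the origin of the planning figures. An interruption rate of MOH can only be computed in patients who have MOH, and section 2.10 already names the source population of 3.0 and 4.5.

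**Conclusion.** The concern holds as a point about precision. The plan enrols a mixed cohort, takes its planning figures from CM with MOH, and governs covariates by a rule that would admit MOH in only about 3% to 4% of 40 v 40 allocations. If change in headache days differs by MOH status, power at 35 per arm falls by about 2 points (2-day gap), 4 points (3 days) or 11 points (5 days); with no gap it does not fall. These figures rest on an assumed MOH share of 50%, an SD of 4.5 within each MOH group, and gaps that the documents do not supply.

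The documents do not support the stronger claims that the list is known to be unstratified, that the mixed-cohort SD must exceed 4.5, or that the result would be biased. The change is worth making because it is nearly free, not because the trial is invalid without it.

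**What to change.** In section 2.10, name baseline MOH status and its interaction with time as fixed terms in the primary model, to be kept whatever the baseline comparison shows. An equivalent choice is a baseline-adjusted analysis of headache days at T4 with MOH as a covariate. For this factor, drop the significance-based selection. If randomisation has not begun, also generate the list separately for patients with and without MOH.

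The cost is one or two model degrees of freedom and, where still possible, a second list. No patients, visits or measurements are added. If randomisation has started, the model term can still be fixed before the data are unblinded.

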### 2.2. Outcome Measures

The primary aim of the present study is to test the efficacy of TNE as a preventive treatment for CM compared to a general education protocol. The primary outcome will be the reduction in monthly headache days from baseline to follow-up. Secondary endpoints will include (i) the interruption rate of MOH; (ii) the proportion of patients achieving a >50% reduction in headache days (i.e., responders) at follow-up; (iii) differences in biomarkers (IDAP, nBR, and the QST) between responders and non-responders, along with the correlation between these biomarker values and clinical improvement in headache day reduction to assess their potential as efficacy predictors; and (iv) significant reductions in disability and migraine burden scores.

### 2.3. Randomization, Schedule, and Adherence

Patients will be randomly assigned at a 1:1 ratio using a pre-generated randomization list created in SPSS by an experimenter who will not be involved in patient recruitment, treatment, or data analysis. Participants will be required to attend a full course of 10 lessons, with the first and last sessions conducted in person and the remaining eight delivered remotely via PowerPoint presentations. Lessons will be held in small groups, with the real and control education groups scheduled on different days to prevent interaction between participants from different study arms. The treatment will be considered valid if patients attend at least 8 out of 10 lessons. In case of absence, the PowerPoint presentation from the missed session will be sent to the participant. Additionally, a brief Q&A session will be conducted before the next lesson to review the content and address any questions.

### 2.4. Study Design

After screening for inclusion/exclusion criteria (T0), patients will complete a headache diary for one month before entering the study (T1). At this point, they will undergo QST, neurophysiological assessments, and questionnaire evaluations before being randomly assigned to either the experimental (TNE-A) or control (CON-A) group (further details provided in the next section).

Following the 5th lecture (T2), patients will repeat the QST and neurophysiological assessment (T2). Headache frequency and questionnaire data will be collected again at the end of the 10-session program (T3). Additionally, headache burden will be reassessed two months after completing the TNE program (T4) (see Figure 1). This protocol follows the Standard Protocol Items: Recommendations for Interventional Trials (SPIRIT) guidelines [39] and is designed and will be reported in accordance with the Consolidated Standards of Reporting Trials (CONSORT) [40].

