Adherence is another critical consideration. Given the duration of the treatment, with several lessons over an extended period, there is a potential risk of high dropout rates. However, our protocol has been designed to make attendance manageable, with only one lesson per week. Eight out of ten lessons can be attended remotely through a conference platform and last about an hour. In three instances, patients are required to admit to the hospital: at T1 to perform baseline assessment and receive the first lesson in presence, midway thought the TNE treatment to collect the second neurophysiology assessment, and at the end for the recap lesson which has the scope of performing a recap of the prior lessons and reinforce the learning. Although attendance is required, it is not as frequent as other protocols, such as neuromodulation treatments, which typically require visits two to three times a week for one to two months. Patients who decide to discontinue the study will be referred to alternative treatments and will be classified as non-responders in the analysis. Regarding the follow-up duration, while some migraine education studies have followed patients for 12 months [57], we opted for a shorter follow-up period, as in other trials [58], in order to grant a good preventive prediction of neurophysiological tests. Longer follow-ups could be influenced by spontaneous fluctuations that may alter the headache profile [59]. In conclusion, despite the complexities of the TNE protocol, the study incorporates strategies to minimize dropouts. The increasing use of TNE in challenging settings, such as for breast cancer patients [60], demonstrates the high feasibility of these approaches.

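### The headache diary runs throughout, but headache days are scheduled only at T1, T3 and T4, so patients who leave during the lessons bring no post-baseline value to the primary model

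*Protocol article*

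**What the plan says.** Section 2.1 (Study Cohort) provides for continuous recording: "Migraine burden will be assessed throughout the study using a headache diary (tracking headache days, pain intensity, and acute medication use" are its opening words on burden.

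Section 2.4 (Study Design) sets the times at which headache is counted:

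- Baseline: "patients will complete a headache diary for one month before entering the study (T1".
- Mid-treatment: "Following the 5th lecture (T2), patients will repeat the QST and neurophysiological assessment (T2". No headache count is named here.
- End of lessons: "Headache frequency and questionnaire data will be collected again at the end of the 10-session program (T3".
- Follow-up: "headache burden will be reassessed two months after completing the TNE program (T4".

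The Abstract is narrower still and places the evaluation of effectiveness at T1 and T4.

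Section 2.10 (Plans for Analysis) analyses the primary outcome with "a generalized linear mixed model for repeated measures", with group, time and their interaction. It does not list the time levels. The Discussion says of the lesson period that "there is a potential risk of high dropout rates", describes steps to limit this, and states that patients who discontinue are counted as non-responders.

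**The concern.** The first scheduled headache count after randomisation is at week 10. For a patient who leaves before then, the model holds only the T1 value and must predict T4 from arm and baseline, as if the patient would have done as well as a completer with the same baseline. The first weeks on treatment are in the diary, and they are a plausible reason for leaving, but the schedule does not turn them into an outcome value.

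The two arms deliver deliberately different content, so unequal loss is possible, although nothing in the article shows that it will occur. If it does occur and follows early lack of benefit, the T4 difference shifts in a direction set by which arm loses more. The non-responder rule serves the responder endpoint only.

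There is a side effect. The Introduction expects biomarker changes at mid-treatment to come before clinical improvement, but the scheduled counts cannot show whether improvement had already begun at T2.

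**Working it through.** **1. The plan's own figures (section 2.10).** Difference 3.0 days, SD 4.5, alpha 5% (taken as two-sided), power 80%:

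n per arm = 2 × (1.960 + 0.842)² × 4.5² / 3.0² = 35.3, or 70.6 in total (72 after rounding each arm up).

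The stated 70 is reproduced to within rounding. Recruiting 80 implies an allowance of 1 − 70/80 = 12.5%, or 5 of 40 per arm if spread evenly. The article gives no rate itself, and the allowance covers the whole study.

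**2. What a leaver with only T1 adds to precision.** Assumptions: SD 4.5 at every time, equal correlation ρ between times, 40 per arm, 5 per arm leaving before T3. The contrast is the between-arm difference in T4 minus T1.

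- Leavers excluded, ρ = 0.5: SE = √[2 × 4.5² × 2(1 − 0.5)/35] = 1.076.
- Leavers' T1 row kept: SE = √{2 × 4.5² × [(1 − 0.5²)/35 + (1 − 0.5)²/40]} = √(2 × 0.5605) = 1.059.

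| ρ | Leavers excluded | T1 row only | Month 1 added | Months 1 and 2 added |
|---|---|---|---|---|
| 0.5 | 1.076 | 1.059 | 1.053 | 1.050 |
| 0.7 | 0.833 | 0.825 | 0.818 | 0.815 |

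The small gain from the T1 row comes through the baseline mean alone. It vanishes if baseline is a covariate or the outcome is change. Diary blocks improve the SE from 1.059 to 1.050 at ρ = 0.5, which is under 1%.

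**3. Bias at T4.** Without early data, each arm's T4 mean is the regression of T4 on T1 in completers, averaged over everyone randomised. With early data, the first diary block is added as a predictor. Assumptions: true difference 3.0, SD 4.5, correlations between blocks 0.5 to 0.75 (0.5 or 0.7 in the 40-per-arm run). Loss is TNE/control. The results come from separate simulations with different set-ups.

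| Loss and driver | Without first block | With first block |
|---|---|---|
| 20%/5%, early change (400,000 per arm) | 3.40 | 2.98 |
| 20%/5%, early change (separate check) | 3.33 | 3.0 |
| 20%/5%, 40 per arm, early change in TNE, random in control | 3.31 (ρ 0.5), 3.29 (ρ 0.7) | 2.99 |
| 5%/20%, early change (400,000 per arm) | 2.59 | 3.00 |
| 5%/20%, early change (separate check) | 2.66 | 3.0 |
| 15%/10%, early change | 3.09 | not reported |
| 12.5%/12.5%, early change | 3.01 | 3.01 |
| 20%/5%, change in weeks 6 to 10 | 3.41 | 3.29 |
| 5%/20%, change in weeks 6 to 10 | 2.60 | 2.73 |

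At 20% versus 5% the early-driven bias is therefore 0.29 to 0.40 day, or 0.29/3.0 = 10% to 0.40/3.0 = 13%. Reversing the arms gives −0.34 to −0.41. At 15% versus 10% it is 0.09 day, and at equal loss about zero.

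Where later change drives leaving, the first block alone removes 0.12 of 0.41 day in one case and 0.13 of 0.40 in the other.

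**The case against.** The strongest reply is that time levels, covariance structure and missing-data method commonly sit in an analysis plan, which is not shown, and that section 2.4 describes visits and does not say that diary days between them are discarded. That stands against one stronger reading, that early diary data cannot inform the analysis. The article does not say so. It does not answer the narrower point: the article names specific times for headache counts, and any plan using more would have to be reconciled with them.

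A reader might also infer that leavers add nothing to the trial. The Discussion contradicts this, because they count in the responder comparison, and in a model with T1 as an outcome row they add slightly to the primary contrast.

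The size of the bias is partly built in. Leaving was made to depend on early change and early change was then put into the model, so full recovery follows from the design. It is not recovered in every case, as the weeks 6 to 10 rows show. The larger figures need a fourfold difference in loss, for which the article gives no basis: both arms have ten sessions, small groups and homework. Even 0.4 day is 0.4/1.06 = 0.38 of the standard error.

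Finally, the article calls dropout a potential risk and describes mitigation; it does not predict losses. It does not say when diaries are handed in, so a leaver's partial diary may not be retrieved. These limits stand and make this an improvement to the plan, with no bias demonstrated.

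**Conclusion.** The point holds in a limited form. On the stated schedule, patients who leave during the lessons have no post-baseline headache-day value in the primary model and contribute almost nothing to the T4 contrast, while diary data that could inform it are being recorded.

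The consequence is conditional. It needs leaving driven by early lack of benefit and loss that differs between arms. Under the assumed SD of 4.5 and correlations of 0.5 to 0.75, the bias is about 0.3 to 0.4 day at 20% versus 5%, about 0.1 day at 15% versus 10%, and none at equal loss. Dropout rates, correlations and the leaving mechanism are all assumptions. The sample size is not affected. The change is worth making because it is cheap and makes the missing-at-random assumption more credible.

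**What to change.** In sections 2.4 and 2.10:

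- Derive headache days from the diary in consecutive blocks: baseline, lessons 1 to 5, lessons 6 to 10, and the first and second month after T3. Scale all to a common length (for example, a 35-day count × 28/35 for 28 days).
- Enter all blocks as time levels, so that each patient contributes up to the last completed block. Keep T4 as the deciding contrast.
- State that diaries of patients who leave are retrieved up to withdrawal.
- Say how the non-responder rule in the Discussion relates to the continuous outcome.

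The cost is wording, modest programming and diary retrieval. With five blocks, an unstructured covariance has 5 × 6/2 = 15 parameters to estimate from 80 patients, so a simpler fallback structure should be named in advance. No additional assessment is needed if the diary is kept as section 2.1 describes.
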